### Sample analysis

Plasma ALT, cystatin C, creatinine and albumin as well as urine A1M and urine creatinine clearance will be analysed using validated clinical routine methods at accredited hospital laboratories. Cloxacillin samples will be centrifuged (2000 g, 10 min) within 1 hour of sampling, aliquoted into 6×500 µL cryotubes and stored in −80°C until analysis. Total and free fraction of cloxacillin will be analysed at Karolinska University Laboratory (Stockholm, Sweden), using ultrafiltration and LC-MS/MS with validated methods available in clinical routine.^45^

Renal tubular damage biomarkers will be analysed from frozen urine at Academic Laboratory (Uppsala, Sweden), where KIM-1 and NGAL will be analysed using commercial sandwich ELISAs (R&D Systems, Bio-Techne, Dublin, Ireland), and urine cystatin C and NAG with a Mindray BS380 chemistry analyser (Mindray Medical International, Shenzhen, China). The reference intervals used will be <0.414 mg/L (cystatin C^46^) and <10 mg/L (A1M). As there is no internationally recognised reference material for KIM-1, NAG and NGAL, the standard interval will be set to two SD above the mean for each assay according to the manufacturer. Additional urine renal damage biomarkers may come to be analysed using validated methods.

On day 30 (28–35), a proportion of the trial subjects will be asked about their experience of the trial through a questionnaire or a brief, semistructured interview to provide feedback on their experience of participation in the trial.

### Trial duration

Trial recruitment was planned to start in January 2024, but was delayed until 15 July 2024. Recruitment finalisation was planned to 31 July 2026 but has been postponed to a preliminary date of 31 December 2026. An interim analysis will be conducted mid-term with the possibility of trial prolongation.

### Endpoints

Primary endpoints:

Proportion of patients with SAB reaching 100% ƒT>MIC_ECOFF_, that is, an unbound cloxacillin trough level of >0.5 mg/L at days 2 and 7 and its association with renal function.Proportion of patients with SAB reaching an unbound cloxacillin trough level of >5 mg/L or total trough level of >50 mg/L at days 2 and 7 and its association with renal function.

Secondary endpoints:

Prevalence of increased levels of urine markers for renal tubular damage (cystatin C, KIM-1, NAG, NGAL, A1M) compared with reference values, and its association with cloxacillin concentrations (peak and trough) at days 2 and 7.Prevalence of AKI based on creatinine, defined by KDIGO, measured daily between days 1 and 7.Onset of new symptoms from the central nervous system (ie, decreased consciousness, seizures, tremor, hallucinations or confusion), with day 1 regarded as baseline, measured daily on days 1–7, in relation to cloxacillin concentrations (peak and trough) at days 2 and 7.Descriptive characteristics of the SAB population, including sex, age, weight, comorbidity, medications, infection severity, complexity, duration and 30-day mortality.Levels of additional exploratory biomarkers in urine and plasma associated with nephrotoxicity or neurotoxicity.The trial participants’ experience taking part in the trial.

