### Statistical analysis

Continuous variables are expressed as mean±SD if normally distributed and as median and IQR if not. Categorical variables are expressed as numbers and percentages.

Primary endpoints are analysed with univariate logistic regression and receiver operating characteristics (ROC) curves. A multivariate logistic regression is performed including all univariate variables with a p<0.1. Results from the multivariate regression are expressed with OR, area under the curve and 95% CI. A p<0.05 will indicate statistical significance. Multiplicity due to interim analysis will be handled using the method suggested by Haybittle-Peto, where a p<0.001 is deemed significant for the interim analysis and <0.05 for the main analysis.^48^

Secondary endpoints are presented demographically and analysed with linear regression for continuous outcomes and logistic regression for dichotomous outcomes. Results should be considered exploratory.

Multiple imputation techniques will be performed if missing data is equal to less than 10% of the total number of data points for the variable.

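### As worded, the urine tubular markers are related to cloxacillin concentration as raised/not raised rather than as levels, which costs power in an exploratory analysis of 95 patients

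*Protocol article*

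**What the plan says.** - **Endpoints, secondary.** The item for cystatin C, KIM-1, NAG, NGAL and A1M is "Prevalence of increased levels of urine markers for renal tubular damage (cystatin C, KIM-1, NAG, NGAL, A1M) compared with reference values, and its association". The exposure named is the drug's peak and trough level on days 2 and 7. Grammatically, the association is that of the prevalence. No cut-off is applied to the concentration in this item.
- **Sample analysis.** Limits are given for urine cystatin C (below 0.414 mg/L) and A1M (below 10 mg/L). For the other three: "As there is no internationally recognised reference material for KIM-1, NAG and NGAL, the standard interval will be set to two SD above the mean", as supplied by each manufacturer.
- **Statistical analysis.** Secondary endpoints are "analysed with linear regression for continuous outcomes and logistic regression for dichotomous outcomes". No endpoint is matched to a model. The section adds: "Results should be considered exploratory".
- **Endpoints, a separate secondary item.** "Levels of additional exploratory biomarkers in urine and plasma associated with nephrotoxicity or neurotoxicity". This is the only biomarker item worded as levels, and it concerns markers other than the five named.

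**The concern.** All five markers are measured as continuous quantities. Replacing each value by above or below a limit discards how far above or below it lies, so a rise that stays wholly on one side counts as no change. Nothing in the protocol shows where the limits fall in an elderly, bacteraemic cohort. If nearly everyone, or nearly no one, exceeds a limit, the logistic model has few patients in one class and little to work with.

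The Introduction gives as an aim to explore whether renal toxicity is associated with unbound cloxacillin concentration. Among the secondary endpoints, the marker item is the only renal one tied to concentration; the AKI item is a prevalence alone. The Introduction also values the markers for possibly showing injury earlier than creatinine, and graded change is what a cut removes. A null result on the cut scale would be hard to read as absence of a concentration-response.

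**Working it through.** **The plan's own figure.** The protocol states no power or precision for the urine markers. Its 95 (38 + 57) is sized for exposure by renal group. Taking 50% versus 20% overexposed, allocation k = 1.5, two-sided 0.05 and 80% power, and applying to the whole group above 45 the 20% that the protocol states for eGFR above 60:

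- Pooled proportion (0.5 + 1.5 × 0.2)/2.5 = 0.32.
- Uncorrected n₁ = [1.960√(1.667 × 0.32 × 0.68) + 0.842√(0.25 + 0.16/1.5)]²/0.30² = 31.5, so 32 + 48 = 80.
- With continuity correction, n₁ = (31.5/4)[1 + √(1 + 2 × 2.5/(31.5 × 1.5 × 0.30))]² = 36.8, so 37 + 56 = 93.

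This is within 2 of 95. No marker assumption enters it, so 95 serves below only as the available sample.

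**Assumptions, none of them in the protocol.** Log marker and log concentration bivariate normal; modest effect; two-sided 0.05; one marker and one concentration at a time; all 95 patients evaluable. The proportion raised, p, is unknown and is varied.

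**Information kept after the cut.** Relative efficiency is E = φ(z_p)²/[p(1 − p)], where φ is the normal density at the cut. At p = 0.5, 0.3989²/0.25 = 0.637. At p = 0.2, 0.2800²/0.16 = 0.490. At p = 0.1, 0.1755²/0.09 = 0.342. At p = 0.05, 0.1031²/0.0475 = 0.224.

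**Detectable correlation at 80% power.** For the continuous marker, r = tanh[(1.960 + 0.842)/√(95 − 3)] = tanh(0.292) = 0.284. For the cut marker, on the underlying scale, approximately 0.284/√E.

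| Raised | E | Loss | 95 × E | Detectable r |
|---|---|---|---|---|
| not cut | 1 | 0 | 95 | 0.28 |
| 50% | 0.637 | 36% | 60.5 | 0.36 |
| 30% or 70% | 0.576 | 42% | 54.7 | 0.37 |
| 20% or 80% | 0.490 | 51% | 46.5 | 0.41 |
| 10% or 90% | 0.342 | 66% | 32.5 | 0.49 |
| 5% or 95% | 0.224 | 78% | 21.3 | not carried this far |

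E is largest at p = 0.5, so under these assumptions the loss is never below 36%. It has no ceiling at 66%.

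**Simulated power, n = 95** (linear test against the score test of the logistic model):

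- True correlation 0.30: about 84–86% continuous, against 64% (50% raised), 61% (30%) and 40% (10%).
- True correlation 0.10: about 15–16% against 8–12%, a gain of 4–7 points.
- True correlation 0.50: about 100% against 94–99% with 20–50% raised, a gain of 1–6 points; about 18 points with 10% raised.

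**The case against.** **The plan does not exclude a continuous analysis.** A reader might infer that the association can be tested only on yes/no outcomes. The protocol does not support that. Linear regression is offered for continuous secondary outcomes without naming them. Only two secondary items are tied to concentration, and the other, new CNS symptoms, is dichotomous, so the markers are natural candidates for the linear model. The abstract also speaks more loosely of renal damage being associated with drug levels. This stands. It leaves the endpoint wording, which fixes the outcome as raised against reference, so a reader who follows it would fit a logistic model. Model detail may be left to an unseen analysis plan; the scale of the endpoint is stated here.

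**The size rests on assumptions.** A reader might also take a 36–66% loss as a fact about this trial. It is not: that range corresponds to 10–90% of patients raised and a normal log marker, neither given in the protocol. Nor is the power gain large in every case, as the correlations of 0.10 and 0.50 show. The model used is also the one that favours linear regression; threshold responses and outliers were not examined.

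**A reference limit answers a real question.** Asking how common abnormal values are is legitimate, and two of the five markers have explicit limits. This stands as a reason to keep the prevalence. It is not a reason to put the association on the same scale.

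**The endpoint is exploratory.** The protocol says so, the trial is not sized for it, and the measured levels remain available. This limits the weight of the point.

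**Conclusion.** The point holds in a limited form. As worded, the endpoint defines the association of the five markers with concentration on a dichotomised outcome, and the linear regression mentioned elsewhere is neither assigned to the markers nor closed to them. Under a roughly normal log marker, a linear relation with log concentration and a modest effect, the cut costs at least 36% of the information at any prevalence, and more as the limit moves away from the middle of the distribution. The benefit of modelling levels is clearest at moderate correlations and small at very weak ones, or at strong ones with a central cut.

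A reader might go further and conclude that the trial's main findings are at risk. They are not: the primary endpoints do not use these markers, and no confirmatory claim depends on this regression. It is a low-severity improvement, worth making because it costs almost nothing.

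**What to change.** In the Endpoints section, keep the proportion above reference for each of the five markers as a descriptive result. Define the exploratory association on the marker level: linear regression of log marker on log cloxacillin concentration, reported as the ratio of geometric means per doubling of concentration with its 95% CI. Use a rank-based or censored (Tobit) method where values lie below the detection limit. In the Statistical analysis section, state that the linear model applies to these markers.

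The cost is wording: no new samples, assays or patients. The small downside is that the association becomes a ratio of levels rather than the odds of exceeding a limit. The retained prevalence still shows how many patients exceed each limit.

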**Methods and analysis:**

This multicentre, prospective, observational clinical trial will include 95 adult patients with methicillin-susceptible *S. aureus* bacteraemia, treated with cloxacillin. Patients with endocarditis, polymicrobial bacteraemia or those considered unsuitable for cloxacillin treatment are excluded. Trough and peak total and unbound cloxacillin concentrations will be measured at steady state at days 2 and 7. Blood cultures will be obtained at days 2, 3, 4 and 7 to assess time to negative culture. Renal function will be assessed daily for plasma creatinine and at days 1 and 6 for cystatin C and for 12-hour urine creatinine clearance. In a novel approach to detecting nephrotoxicity, renal tubular damage biomarkers will be measured at days 1 and 6 (KIM-1, N-acetyl-β-D-glucosaminidase, neutrophil gelatinase-associated lipocalin, urine cystatin C, alpha-1-microglobulin). Detection of neurologic symptoms such as confusion, tremor, hallucinations and convulsions, as well as consciousness, will be monitored daily using a structured evaluation form.

We aim to investigate to which extent target attainment (100% of the dosing interval during which the free (unbound) drug concentration exceeds the minimum inhibitory concentration) is achieved with standard dosing of cloxacillin in a real-world cohort of hospitalised patients with SAB, and whether initial renal function can predict who is at risk for underdosing or overdosing. We will also explore whether neurological or renal damage is prevalent and associated with cloxacillin levels.

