Most therapeutic drug monitoring studies of cloxacillin involve critically ill patients with SAB in the intensive care unit (ICU) or patients with infective endocarditis.^14^,^16^ However, the typical patient with SAB is older (66–75 years) without endocarditis and is treated outside of the ICU.^17^,^20^ In younger patients outside the ICU, a small study in which total concentrations were measured suggests a low probability of achieving 100% fT>MIC with intermittent cloxacillin dosing regimens.^21^ However, these results may not be applicable to an elderly population, among whom an increased prevalence of chronic kidney disease can be anticipated,^22^ since augmented renal clearance is a risk factor for insufficient exposure of beta-lactam antibiotics.^23^ Estimation of renal function has shown potential in identifying insufficient exposure among ICU patients for some low-to-medium protein bound beta-lactam antibiotics,^24^ but the relevance for highly protein bound antibiotics among patients with SAB outside of the ICU is unknown.

Acute kidney injury (AKI) is common for patients with SAB, with a reported incidence between 17% and 43%, and is associated with an increased 30-day mortality.^25^,^27^ Although AKI has been considered to be caused by the infection per se, treatment with isoxazolyl penicillins has also been associated with an increased risk of nephrotoxicity.^28^ There are limited data on whether the increased risk of isoxazolyl penicillin-induced AKI is concentration-dependent, but small studies suggest that about 57%–71% of patients with manifest AKI had a cloxacillin concentration above 50 mg/L.^29 30^ The reported median time of AKI recovery after cloxacillin cessation is 5 days, which implies that early detection of AKI is beneficial for timely dose adjustment.^29^ However, an increase of serum creatinine as a routine marker for kidney injury is rarely detected until 1–2 days after AKI onset. AKI onset usually occurs within days after therapy initiation,^29^ suggesting the development of acute tubular necrosis.^29 31^ Biomarkers of renal tubular injury may have the potential to detect AKI at an earlier stage than serum creatinine,^32^ but their diagnostic potential has not been widely evaluated in patients treated with beta-lactam antibiotics.^33^

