Recent findings suggest that high concentrations of beta-lactam antibiotics may be associated with neurologic symptoms, including persistent coma and delirium, resulting in longer hospital stays.^16 34 35^ A small study reported that neurologic symptoms in critically ill patients improved for all patients after dose reduction of cloxacillin.^16^ It is therefore important to identify whether neurological symptoms may be associated with antibiotic concentration levels, including non-ICU patients with SAB. We plan to conduct a prospective observational study in a real-world, hospitalised population with SAB. The study is approved as a low-interventional clinical trial registered in CTIS (Trial registration number: EUCT 2023-505148-20-00).

We aim to investigate to which extent target attainment (100% fT>MIC) is achieved with standard dosing of cloxacillin in a real-world cohort of hospitalised patients with SAB, and whether initial renal function can predict who is at risk for underdosing or overdosing. Furthermore, we will explore whether renal- or neurotoxicity may be associated with unbound cloxacillin concentrations, including the potential for novel renal tubular damage biomarkers to identify beta-lactam induced AKI. Lastly, we will survey the trial participants’ experience of taking part in the trial.

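### The toxicity endpoints also use a day-7 cloxacillin level drawn after most of the outcomes, so earlier renal injury can look like cloxacillin toxicity

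*Protocol article*

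**What the plan says.** The Abstract states that "renal tubular damage biomarkers will be measured at days 1 and 6", and that "Trough and peak total and unbound cloxacillin concentrations will be measured at steady state at days 2 and 7". Table 2 (Trial procedures) gives the same days.

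Under Endpoints, three secondary items bear on toxicity:
- Tubular markers: prevalence of values above reference, and "its association with cloxacillin concentrations (peak and trough) at days 2 and 7".
- CNS symptoms: new onset, "with day 1 regarded as baseline, measured daily on days 1–7, in relation to cloxacillin concentrations (peak and trough) at days 2 and 7".
- AKI: "Prevalence of AKI based on creatinine, defined by KDIGO, measured daily between days 1 and 7". This item mentions no concentration. The link between AKI and levels comes from the aim in the Introduction: "we will explore whether renal- or neurotoxicity may be associated with unbound cloxacillin concentrations".

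Statistical analysis specifies linear or logistic regression for secondary endpoints and calls the results exploratory. Nothing in the article limits these associations to levels drawn before the outcome.

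**The concern.** An association read as toxicity needs the exposure to come before the outcome. For the day-7 level this often fails, and the protocol itself describes a route by which the outcome could drive the exposure. It assumes that levels above the toxicity threshold occur in 50% of patients with eGFR ≤45 mL/min/1.73 m² but in 20% of those above 60 (Hypothesis and sample size calculations). The Background reports AKI in 17%–43% of patients with this infection, places its onset within days of starting therapy, and notes that it has been attributed to the infection.

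Infection-driven renal injury before day 7 could therefore lower clearance, raise the day-7 level and produce a positive association even if cloxacillin were harmless. What is at stake is the stated aim of relating renal and neurological toxicity to unbound concentration.

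**Working it through.** **Order of measurements** (Abstract, Table 2, Endpoints)

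| Outcome | Day-2 level | Day-7 level |
|---|---|---|
| Day-1 marker | level after outcome | level after outcome |
| Day-6 marker | **level before outcome** | level after outcome |
| CNS onset on days 3–6 | **level before outcome** | level after outcome |
| CNS onset on day 2 | depends on the hour | level after outcome |
| CNS onset on day 7 | **level before outcome** | depends on the hour |

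Of the four marker–level pairs, one is correctly ordered.

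**Size, illustration 1: shift in the day-7 trough.** The plan gives no figure for this, so there is none to reproduce. This check tests the day-7 level by AKI with no toxicity at all.

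- From the protocol: n = 95; AKI 17%–43%, so 0.17 × 95 ≈ 16 against 79 patients, or 0.43 × 95 ≈ 41 against 54.
- Assumed: log-trough SD 0.7 between and 0.4 within patients; AKI multiplies the day-7 trough by f = 1.1, 1.3, 1.5 or 2.
- Total SD = √(0.7² + 0.4²) = √0.65 = 0.806.
- SE = 0.806 × √(1/n₁ + 1/n₂) = 0.221 for 16/79 and 0.167 for 41/54.
- Noncentrality δ = ln(f)/SE; rejection probability from the noncentral t with 93 df, two-sided 5%.

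| f | ln f | δ (16/79) | δ (41/54) | Rejection |
|---|---|---|---|---|
| 1.1 | 0.095 | 0.43 | 0.57 | 7%–9% |
| 1.3 | 0.262 | 1.19 | 1.57 | 22%–34% |
| 1.5 | 0.405 | 1.83 | 2.43 | 44%–67% |
| 2 | 0.693 | 3.14 | 4.15 | 87%–98% |

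Simulation under the same assumptions gave 8%–9%, 20%–34%, 44%–66% and 86%–98%, which agrees to within about 2 percentage points.

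**Size, illustration 2: the protocol's own rates.** Suppose uninjured patients have a 20% chance of a level above 5 mg/L and injury moves a patient to 50%. The odds ratio with no toxicity is (0.5/0.5)/(0.2/0.8) = 4.0, and Fisher's exact test gives p<0.05 in 65% (16/79) to 85% (41/54) of trials. If only half of the injured patients shift, the probability is 0.20 + 0.5 × 0.30 = 0.35, OR = (0.35/0.65)/0.25 = 2.15, and rejection is 24%–33%. If a quarter shift, it is 0.275, OR 1.52 and 10%–11%. With no shift, Fisher's test rejects in 3%–4%.

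**The case against.** Several objections have force.

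- **The right analysis is already there.** The endpoints name day 2 as well as day 7. A reader might infer that every toxicity outcome is set against a later level. The text does not support that: it neither fixes same-visit pairing nor excludes the day-2 level. Pairing could in principle be settled in a fuller document, but the endpoint as published expressly includes the day-7 level, so this part is more than missing detail.
- **The figures concern AKI, not the quoted endpoint.** Endpoints lists AKI as prevalence only, and tubular marker elevation need not lower filtration. The figures do not carry over directly to markers or symptoms. This stands.
- **The rises are assumed.** Neither the fold changes nor the SDs are in the protocol, and dose changes after AKI could make the net rise smaller. This stands, and is why the range starts at 1.1-fold.
- **Day 2 is not guaranteed clean.** Cloxacillin may start up to 72 hours before inclusion (Table 1), so injury can precede and raise the day-2 level too. A 1.3-fold rise there would give the same 22%–34%. This stands, and it is why the remedy needs patients event-free at that sample and adjustment for day-1 eGFR.
- **CNS symptoms do not raise levels.** A reader might infer reverse causation here as well. The problem is instead wrong time order and illness that affects both symptoms and clearance. A level raised by renal injury is also real exposure for symptoms that come later.
- **Reference values.** Comparing markers with reference limits is a legitimate definition of prevalence and is not an error.
- **The results are exploratory.** That tempers inference and limits the consequence, since no primary endpoint or sample size depends on these results. It does not remove a bias with a predictable direction, which more patients would not reduce.

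**Conclusion.** The point holds for the day-7 level. Its association with day-6 markers, or with symptoms that began earlier, has the exposure measured after the outcome. For renal outcomes the protocol's own expectations supply a path from injury to level, so injury can look like toxicity. Whether it will, and how strongly, cannot be read from the protocol. For AKI set against the day-7 level, the false-positive rate runs from little above nominal (7%–9% at a 1.1-fold rise) to 87%–98% at a 2-fold rise, under the assumed SDs and no true toxicity. The upper end should not be quoted alone as the expected error.

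The day-2 level against later outcomes is correctly ordered, though still open to confounding by baseline renal function. These are secondary, exploratory endpoints, so the change is advisable and does not affect the trial's main conclusions.

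**What to change.** Amend the secondary endpoints and their analysis as follows:

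1. Name the day-2 unbound level as the exposure for the toxicity associations.
2. Markers: regress the log day-6 marker on the log day-2 level, adjusted for the log day-1 marker and day-1 eGFR.
3. CNS symptoms, and AKI if it is analysed against levels: relate the day-2 level to first onset after the day-2 sample, in patients event-free at that time, adjusted for day-1 eGFR.
4. Keep prevalence against reference values as the descriptive endpoint.
5. Report associations of day-7 levels with earlier outcomes as descriptive, and state that they are not evidence of toxicity.

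The cost is wording only, since all the data are already collected. There are two downsides. Events before the day-2 sample leave the association analysis, and these may include some early drug-related injury. Day 1 may follow up to 72 hours of cloxacillin, so adjusting for day-1 values does not give a drug-free baseline, and the report should say so.

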### Trial population

The trial population will consist of adult patients with a blood culture with growth of *Staphylococcus aureus,* obtained no more than 72 hours prior to inclusion. The participant is treated with cloxacillin therapy started at the time of, or no more than 72 hours prior to, inclusion, and has given informed consent. Inclusion and exclusion criteria are found in table 1. Patients will be treated with standard-of-care according to the treating physician, normally intravenous cloxacillin 2 g every 6–8 hours for at least 7 days.

**Table 1 T1:** Inclusion and exclusion criteria

Inclusion criteria	Exclusion criteria
Positive blood culture with *Staphylococcus aureus* obtained no more than 72 hours before inclusion	*S. aureus* not susceptible (S) to cloxacillin
≥18 years of age	Polymicrobial bacteraemia or concomitant infection which demands treatment with an antibiotic with broader spectrum than cloxacillin.
Treatment with cloxacillin, started at inclusion or no more than 72 hours before inclusion	Endocarditis or other intracardial infections detected by echocardiography.
Informed oral and written consent	Serious allergic reaction to cloxacillin, other penicillins or cephalosporins.
	Any contraindication for cloxacillin treatment or trial participation as judged by the treating physician.
	Moribund; when a cure is not deemed achievable with active treatment and aim of care is to give end-of-life or best supportive care
	Breastfeeding and not able or willing to interrupt breastfeeding
	Unconsciousness, not willing to participate or assessed as having difficulties understanding the significance of trial participation due to mental disability or language barriers.
	Participation in a clinical trial 30 days prior to initiation
	Prior participation in the current trial

Cloxacillin susceptibility is assessed using clinical break-points from 2025 by the European Committee on Antimicrobial Susceptibility Testing (EUCAST).^5^

Participants with no available echocardiography at the time of inclusion may still be recruited. If endocarditis is detected with echocardiography later during the trial, the participant will be excluded.

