### Trial procedures

The trial duration for each participant will be 30 days. Initial blood and urine sampling will occur during the first 7 in-hospital days, and outcome data will be gathered on day 30 from the medical record (table 2).

Each positive blood culture will be reported to an infection specialist by direct contact from the microbiology lab at each site. Eligibility of trial participation will be assessed, where eligible patients are informed about and asked to participate in the trial by a doctor or nurse associated with the trial. After written informed consent is obtained, participant characteristics are registered (gender, age, weight, height). Comorbidity will be estimated using the Charlson comorbidity index.^37^ Infection severity will be estimated via the National Early Warning Score 2.^38^ Current medications and dosing at time of inclusion will be recorded as will any addition, withdrawal or dosing adjustments during the trial duration. Prevalence of neurologic symptoms will be registered with occurrence of tremor, hallucination, convulsions or confusion corresponding to ≥2 points measured by Nursing Delirium Screening Scale,^39^ as well as consciousness level assessed using the Reaction Level Scale-85.^40^ Blood cloxacillin concentrations will be sampled prior to administration (trough) as well as within 30 min after end of cloxacillin infusion (peak) (table 2). Additional measurements of plasma liver and renal biomarkers (alanine aminotransferase (ALT), cystatin C, creatinine and albumin) and blood cultures (aerobic+anaerobic) will be sampled at the same time as clinical sampling or trough level sampling.

**Table 2 T2:** Trial procedures

Procedures	Day							
	1	2	3	4	5	6	7	30 (28–35)
Inclusion/exclusion criteria eligibility	√							
Informed consent	√							
Demographic and clinical data, comorbidity, current medication, baseline symptoms CNS	√							
Neurological symptoms, NEWS-2, medication and dosing adjustments	√	√	√	√	√	√	√	
Plasma samples: ALT, cystatin C, albumin.	√					√		
Plasma creatinine, eGFR estimation	√	√	√	√	√	√	√	
Urine sample for renal damage marker measurement and initiation of 12 hours urine sampling for creatinine clearance measurement	√					√		
Plasma samples for cloxacillin-concentration measurement (peak and trough) and urine creatinine measurement with creatinine clearance calculation		√					√	
Blood culture		√	√	√			√	
Final diagnosis, duration of bacteraemia, mortality, complexity of infection								√

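### The day-6 tubular markers have only one later study creatinine, less than the 1–2 day lag the protocol states, so their value for early detection of AKI can barely be tested

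*Protocol article*

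**What the plan says.** - **AKI endpoint** (Endpoints, secondary): "Prevalence of AKI based on creatinine, defined by KDIGO, measured daily between days 1 and 7". The Table 2 row "Plasma creatinine, eGFR estimation" is ticked on days 1 to 7 and not on day 30.
- **Tubular markers** (Abstract, Methods and analysis): "renal tubular damage biomarkers will be measured at days 1 and 6". Table 2 agrees.
- **Why the markers are studied** (Background): "an increase of serum creatinine as a routine marker for kidney injury is rarely detected until 1–2 days after AKI onset".
- **Aim** (end of Background): toxicity will be explored, "including the potential for novel renal tubular damage biomarkers to identify beta-lactam induced AKI".
- **Expected timing of AKI** (Background): "AKI onset usually occurs within days after therapy initiation".
- **Treatment** (Trial population): "normally intravenous cloxacillin 2 g every 6–8 hours for at least 7 days". Cloxacillin may have started up to 72 hours before inclusion.
- **Late follow-up** (Trial procedures): "outcome data will be gathered on day 30 from the medical record". The items listed are mortality, loss to follow-up, time to negative culture, SAB complexity and diagnosis codes. Creatinine and renal replacement therapy are not among them.
- **Status** (Statistical analysis): results for secondary endpoints are exploratory.

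**The concern.** The case for the markers is that they may show injury before creatinine does. Testing this requires creatinine to be followed after each marker sample for at least as long as the lag. The protocol puts the lag at 1–2 days but follows creatinine for only one day after the second and last marker sample.

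The day-6 sample matters most for injury caused by the drug. Day 1 falls at, or within about 72 hours of, the start of cloxacillin, and the Background section notes that AKI in SAB has been attributed to the infection itself. A raised marker on day 1 may therefore largely reflect infection. Day 6 is the only marker sample after sustained exposure, and it has the shorter outcome window.

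At stake is one exploratory aim. If day-6 markers are raised and creatinine has not moved by day 7, the data cannot separate injury that creatinine has yet to show from a marker rise without AKI.

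**Working it through.** The plan gives no figure of its own on this point. Its one computed design figure, 38 + 57 = 95 patients, concerns cloxacillin exposure by renal function and does not enter here. The check is calendar arithmetic.

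**Inputs.** Marker days 1 and 6 (Abstract, Table 2). Last study creatinine on day 7 (Endpoints, Table 2). Lag of 1 to 2 days (Background). Cloxacillin start 0 to 72 hours before inclusion (Table 1). Assumption: trial day 1 is the day of inclusion.

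**Step 1. Creatinine follow-up after each marker sample** = last creatinine day − marker day.
- Day-1 sample: 7 − 1 = 6 daily values.
- Day-6 sample: 7 − 6 = 1 daily value.

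**Step 2. Latest AKI onset that study creatinine can show** = last creatinine day − lag.

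| Last creatinine | Lag 1 day | Lag 2 days | Covers onset on day 6? |
|---|---|---|---|
| Day 7 (as planned) | day 6 | day 5 | only at a 1-day lag |
| Day 8 | day 7 | day 6 | yes, at both lags |
| Day 9 | day 8 | day 7 | yes, at both lags |

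As planned, onset on day 6 is visible only at the lower end of the lag, and onset on day 7 or later is not visible at either end. Day 8 is the shortest extension that gives a day-6 onset the full stated lag.

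**Step 3. Trial days as treatment days.** With a start 0 to 72 hours before inclusion, trial day 1 is treatment day 1 to about 4, and trial day 7 is treatment day 7 to about 10. Treatment normally lasts seven days or longer, so some patients will still be on cloxacillin when creatinine collection ends.

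**Step 4. Can the number affected be computed?** The Background section cites an AKI incidence in SAB of 17% to 43%. Applied to 95 patients, this is 95 × 0.17 = 16.2 to 95 × 0.43 = 40.9, or about 16 to 41 cases in all. The documents do not say how onset is spread over time, so the share first visible after day 7 cannot be derived.

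**The case against.** The strongest defence has four parts.

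1. **The window is declared.** The AKI endpoint is openly limited to days 1–7 and matches Table 2. AKI after day 7 is outside the endpoint by definition. This stands: the endpoint is bounded, not wrong.
2. **No marker-versus-AKI analysis is defined.** The marker endpoint compares markers with reference values and relates them to cloxacillin concentrations. AKI prevalence is a separate endpoint. A reader might infer that day-6 markers will be scored as false positives and so biased towards looking useless, but no such analysis is specified. What remains is the aim at the end of Background, which the day-6 sample can hardly serve as early detection.
3. **Some checking is possible.** A reader might infer that the markers cannot be checked at all. That is too strong. Day-7 creatinine follows the day-6 sample at the lower end of the lag, day-1 markers have six later values, and day-6 markers can be compared with AKI already present. Day-30 diagnosis codes may also pick up some later AKI, though not by KDIGO creatinine criteria.
4. **Onset is expected early.** A reader might spread onset evenly over days 1–7 and count 1/7 to 2/7 of cases as hidden: 16.2 × 1/7 = 2.3 up to 40.9 × 2/7 = 11.7. The documents do not support this. They expect onset within days of starting therapy, and trial days 6–7 may be treatment days 9–10, so later onset should be less common. A lag also brings onsets from before day 1 into view, so counting losses at the end alone overstates the net effect.

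Nor do the documents show that a 7-day figure is not comparable with the cited 17%–43%. The observation windows of those studies are not given, and no such comparison is planned.

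None of this removes the mismatch between one day of follow-up and a lag of one to two days.

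**Conclusion.** The point holds in a limited form. The only marker sample after sustained cloxacillin exposure has one later creatinine value, one day short of the upper end of the lag that the protocol gives as its reason for studying the markers. Early detection of AKI from the day-6 sample is barely testable. From the day-1 sample it is testable over six later values, but that sample says less about injury caused by the drug. AKI first visible after day 7 during continued treatment is not captured by study creatinine, and its frequency cannot be computed from the documents.

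This rests on the protocol's own lag and on trial day 1 being the day of inclusion. It concerns an exploratory aim only. The days 1–7 AKI endpoint, the primary endpoints and the sample size of 95 stand as they are.

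**What to change.** Keep the KDIGO endpoint on days 1–7 as planned. Then:

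1. At the existing day-30 record review, also record routine plasma creatinine values after day 7 (at least to day 8, preferably to two days after cloxacillin stops, and no later than the review), any renal replacement therapy, and the cloxacillin stop date.
2. Add a supplementary exploratory analysis:
   - day-6 markers against AKI first met after day 6, in patients free of AKI on day 6;
   - day-1 markers against AKI first met on days 2–7, in patients free of AKI on day 1.

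   State which reference creatinine defines being free of AKI.
3. Report how many patients have a creatinine value after day 7, and how far the values extend.
4. If those values are too sparse, rest conclusions about early detection on the day-1 markers, and state that the day-6 markers have one day of follow-up.

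**Cost.** A few eCRF fields at a review that already takes place, with no new samples. **Drawback.** Creatinine after day 7 is measured on clinical indication, so patients without later tests cannot be classified and ascertainment is uneven. For that reason the analysis should stay supplementary and be labelled so.
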